## Abstract

**Background:**

We present the design of an open randomized multi-centre study on surgical versus conservative treatment of acute Achilles tendon ruptures. The study is designed to evaluate the effectiveness of conservative treatment in reducing complications when treating acute Achilles tendon rupture.

**Methods/Design:**

At least 72 patients with acute Achilles tendon rupture will be randomized to minimally invasive surgical repair followed by functional rehabilitation using tape bandage or conservative treatment followed by functional rehabilitation with use of a functional bracing system. Both treatment arms use a 7 weeks post-rupture rehabilitation protocol. Four hospitals in the Netherlands will participate. Primary end-point will be reduction in complications other than re-rupture. Secondary end-point will be re-rupturing, time off work, sporting activity post rupture, functional outcome by Leppilahti score and patient satisfaction. Patient follow-up will be 12 month.

**Discussion:**

By making this design study we wish to contribute to more profound research on AT rupture treatment and prevent publication bias for this open-labelled randomized trial.

**Trial registration:**

ISRCTN50141196

## Background

Controversy continues with regard to the optimal treatment for acute subcutaneous Achilles tendon (AT) ruptures. Treatment can be classified into operative (open or minimally invasive/percutaneous) and non-operative. Post operative splintage can be divided into cast immobilisation and functional bracing.

Traditionally open surgical repair of a ruptured Achilles tendon has been the first choice of treatment due to low re-rupture rates and the possibility for functional post-operative splintage [1-4]. But, 34% of patients treated with open repair suffer from complications other than re-rupture, especially wound infection and adhesions [1-5]. In general, the outcome after treatment of a re-rupture is poor, but results following treatment of a deep infection are devastating [6]. Therefore an effort should be made to prevent infectious complications. Many articles on different types of minimally invasive repair techniques (using limited incisions or performed percutaneously) of ruptured AT's have been published [7-14]. But to date, only two 2 randomized trials have been reported [4,15]. In Khan's review on randomized trials complications other than re-rupture were substantially reduced with percutaneous repair techniques but data were very limited. Data on complications using limited incision techniques are even more scant. As minimally invasive techniques differ it is hard to compare other techniques with these numbers. An advantage of most minimally invasive techniques is smaller scars and less damage to the delicate blood supply of the AT. Importantly, in most patients minimally invasive surgery does allow functional rehabilitation [7]. Patients treated by functional rehabilitation after operation rather than cast immobilisation are reported to have a shorter in-patient stay, less time off work and a quicker return to sporting activities. In addition, lower complication rates, including re-ruptures, are reported [1-5].

The main advantage of conservative, i.e. non-operative treatment is elimination of wound complications and intra-operative sural nerve damage. Complications other than re-rupture are reported to reduce to 3% [5]. But, conservative treatment with cast immobilisation has shown to increase the re-rupture rate [1,5] and cast immobilisation induces delayed recovery due to calf muscle weakness as a result of long immobilisation of the ankle joint. In contrast, conservative treatment by functional bracing does allow immediate weight bearing, preventing calf muscle weakness and enabling fast recovery. In three studies conservative treatment of AT rupture with functional bracing did not result in increased re-rupture rates [16-18]. But since only one of these is a randomized trial [17], more high quality data from randomized prospective studies is needed. We hypothesized that compared to surgical treatment, conservative treatment with functional bracing will reduce the absolute risk of complications other than re-rupture with 30%.

## Methods/Design

### Design of study

#### Context

The efficacy of minimally-invasive surgery versus functional conservative treatment of acute subcutaneous Achilles tendon ruptures will be studied in a randomized trial. Four hospitals in the Netherlands will participate in the study, one of them being a university medical centre. The Medical Research Ethics Committee of all the participating hospitals approved the study protocol.

#### Patient selection and informed consent

All patients who report to the emergency department of one of the participating hospitals with an acute Achilles tendon rupture will be considered for entering the study protocol. Inclusion and exclusion criteria are listed in table 1 and will be checked by an emergency room doctor, surgical resident or surgeon. All eligible patients are asked to provide written informed consent.

**Table 1 T1:** Inclusion and exclusion criteria

**Inclusion Criteria**	**Exclusion criteria**
Achilles tendon rupture.	Re-rupture/bilateral rupture/open rupture.
Treatment starts within 72 hours.	Combination with fracture of foot or ankle.
Diagnoses by physical examination: palpable gap and calf muscle squeeze test.	Former application (injection) of local corticosteroids in tendon area.
Age 18–65 years.	Contra-indications for surgery.
Written informed consent.	Physical or mental handicaps that do not allow functional treatment or otherwise interfere with the ability to follow-up on the study protocol.

#### Randomisation and concealment

Randomisation is concealed by a specially designed internet site. Randomisation is in blocks (4 blocks) and stratified by centre. The treatment nature is open labelled for patients, physicians and physiotherapists. During follow-up visits physical examination reveals the allocated treatment to patient and assessor.

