#### Sample size

Sample size is calculated on the basis of complication other than re-rupture. With conservative treatment using this new type of functional bracing we hypothesized a 30% reduction in the absolute risk for complications other than re-rupture. This risk reduction is similar to the risk reduction obtained in the systematic review on open versus conservative treatment by Khan: risk of complications for open repair being 34% [5]. Prospective data on the risk of complications of minimally invasive repair is very scant. The Khan review provides the best empirical estimate for the complication risk associated with surgical repair. Therefore we decided to use this risk estimate of complications of open repair for the sample size calculation. With a one-sided α of 0.05, a statistical power of (1-β) of 0.80, and an attrition rate of 10% we need to randomize at least 36 patients per treatment arm.

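### An apparently fixed block scheme, published and applied within centre in an open-label trial, leaves part of the allocation sequence predictable, so web concealment alone does not exclude selection bias

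*Protocol article*

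**What the plan says.** The section Randomisation and concealment of the protocol article makes four statements that have to be read together:

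- Concealment: "Randomisation is concealed by a specially designed internet site".
- Scheme: "Randomisation is in blocks (4 blocks) and stratified by centre". No random or varying block size is mentioned.
- Blinding: "The treatment nature is open labelled for patients, physicians and physiotherapists".
- Assessment: "During follow-up visits physical examination reveals the allocated treatment to patient and assessor".

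Under Context: "Four hospitals in the Netherlands will participate in the study, one of them being a university medical centre". There are therefore four strata. Under Patient selection and informed consent, the eligibility criteria "will be checked by an emergency room doctor, surgical resident or surgeon". One exclusion reads "Physical or mental handicaps that do not allow functional treatment or otherwise interfere with the ability to follow-up on the study protocol", and another is the presence of contra-indications for surgery. Treatment must begin within 72 hours, and every eligible patient is to be asked for consent. Under Sample size: "we need to randomize at least 36 patients per treatment arm".

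**The concern.** Hiding the list is only half of allocation concealment. In a permuted block the arms must balance by the end of the block, so earlier allocations carry information about later ones. That information is harmless if recruiters cannot see earlier allocations or do not know the block structure. Here treatment is open, the strata are single hospitals, and the scheme is in print. A member of staff who follows the hospital's recent patients could know, or guess better than chance, which arm comes next before deciding whether the patient in front of them is eligible.

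The two exclusions that need judgement bear on the arms: fitness for surgery on one side, ability to follow functional treatment on the other. Someone who expects surgery next could apply the first more strictly. With 36 patients per arm, one patient is 1/36 = 2.8 percentage points of an arm, so a few selectively enrolled patients could shift the comparison of complication rates. Outcome assessment is also unblinded, so it does not compensate for unlike groups.

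**Working it through.** The document gives no figure for predictability, so there is nothing of its own to reproduce.

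**Inputs.** Allocation is 1:1 with 36 per arm, hence 72 in total (Sample size). There are four centres (Context). Equal recruitment is an assumption: 72/4 = 18 patients per centre. Block size is not stated unambiguously, so several values are shown.

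**Measures.** An allocation is *certain* when one arm has no places left in the block. The *guess rate* is the share of allocations predicted correctly by always naming the arm with more places left, with a coin toss when the arms are level. Simple randomisation gives 0% and 50%.

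**Block of 4, position by position.**

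| Position | Probability that it is certain | Probability of a correct guess |
|---|---|---|
| 1 | 0 | 1/2 |
| 2 | 0 | 2/3 |
| 3 | 1/3 (first two in the same arm) | 1/3 × 1 + 2/3 × 1/2 = 2/3 |
| 4 | 1 | 1 |
| Sum | 4/3 | 2.833 |

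Over complete blocks, 1.333/4 = 33.3% are certain and 2.833/4 = 70.8% are guessed correctly.

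Eighteen patients fill four blocks and the first two positions of a fifth:

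- Certain: 4 × 1.333 = 5.33 per centre. 5.33/18 = 29.6%, and 4 × 5.33 = 21.3 of 72.
- Guessed: 4 × 2.833 + 1/2 + 2/3 = 12.5 per centre, and 12.5/18 = 69.4%.

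**General block of size B = 2m.** The expected number of certain allocations is 2m/(m + 1), so their share is 1/(m + 1). The expected number of correct guesses is m + (4^m / C(2m, m) − 1)/2. For m = 2 this is 2 + (16/6 − 1)/2 = 2.833, as in the table. For m = 9 it is 9 + (262144/48620 − 1)/2 = 11.196, and 11.196/18 = 62.2%.

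| Block size (complete blocks) | Certain | Guessed correctly |
|---|---|---|
| 4 | 33.3% | 70.8% |
| 6 | 25% | 68.3% |
| 8 | 20% | 66.6% |
| 18 (one block per centre) | 10% (1.8 per centre, 7.2 of 72) | 62.2% |

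**Randomly varying sizes.** These were simulated over 18 patients per centre with 5,000 repetitions. The guesser knows the possible sizes but not the current one.

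| Scheme | Certain | Guessed correctly |
|---|---|---|
| Fixed 4 | 29.7% | 69.4% |
| Random 4 and 6 | 5.7% | 68.4% |
| Random 4, 6 and 8 | 2.3% | 67.0% |

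The guess rate hardly moves for a simple reason. Whatever the block sizes, the best guess is the arm that is behind in the centre so far, and that needs no knowledge of the sizes. What varying the size removes is certainty.

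**The case against.** The strongest reply is that neither a block size nor a fixed size is actually stated. Read literally, the parenthesis gives a number of blocks, and four happens to match the number of hospitals. A condensed article may leave block composition to the full protocol, so silence on varying sizes is not in itself an error. This largely stands: the figure for certain allocations differs threefold between the two readings, and *fixed* is an inference. What remains is that the article chose to publish a blocking parameter and did so ambiguously. On every fixed-size reading tried, predictability is above chance.

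The second reply is that the protocol leaves little room to act on a prediction. Patients present as emergencies and treatment must start within 72 hours, so deferring someone to a later slot is hard. Not offering consent to an eligible patient would breach the protocol. Both points stand as limits, but neither covers the exclusions that rest on judgement, where a decision can be made without any visible breach.

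The third reply concerns outcome assessment. Complications are recorded by a surgeon or resident to tabulated definitions, and deep vein thrombosis needs ultrasound signs. The article does not say that the person who recruits also assesses. That is correct. Unblinded assessment is a separate matter, and here it means only that nothing downstream offsets a selection effect.

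A reader might go further and infer that the website fails to conceal allocation, or that recruiters knew a third of the sequence. The document supports neither. Central web allocation hides the list and blocks direct tampering. Nothing shows that staff tracked their centre's sequence or knew the scheme while enrolling.

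**Conclusion.** The point holds as an avoidable design risk, not as demonstrated bias. A blocking parameter is published, blocking is within hospital, treatment is open, and local clinical staff screen, so part of the sequence can be inferred and web concealment alone does not exclude selection bias.

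Its size depends on the meaning of the parenthesis. If blocks are a fixed 4, about 30% of allocations are certain (about 21 of 72) and about 69% guessable, or 33% and 71% over complete blocks. With one block of 18 per centre, 10% are certain and 62% guessable. These figures assume 1:1 blocks of constant size, a recruiter who follows every earlier allocation in the hospital and knows the block size, and, for the counts out of 72, equal recruitment of 18 per centre. They measure what could be predicted, not how far the treatment comparison would be biased, which the document gives no means to estimate. The change is worth making because it is cheap, but the trial is not invalid without it.

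**What to change.** 1. State what the parenthesis means: a block size, or a number of blocks and of what length.
2. Have the existing website use randomly varying permuted block sizes within centre, for example 4 and 6. If recruitment has begun, as the past tense in parts of the article suggests it may have, apply this to all remaining patients and record the date of the change.
3. Withhold the sizes from recruiting staff, and say in public documents only that sizes vary.

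This should cut certain allocations from about 30% to about 6% if blocks are now a fixed 4, and fewer still if staff do not know the candidate sizes. It should not be presented as making the sequence unguessable: the average rate of correct guesses stays near 68%. The cost is a parameter change in a system already in use. An unfinished block of 6 could leave a centre out of balance by up to 3 patients, against up to 2 with blocks of 4.

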#### Interventions

Surgical therapy consists of a minimally invasive technique (Figure 1) [7]. The same protocol for the operative procedure was used by all surgeons and residents in the participating hospitals. Also, before study participation all surgeons were familiar with the operative procedure. A less than 5 cm longitudinal incision is made over the posterior aspect of the affected leg just proximal to the rupture site. The incision is slightly medially placed. The subcutaneous fat is divided and the peritendineum opened. Then a Bunell type suture is placed though the proximal end of the Achilles tendon (PDS 1.0). With a hollow mandarin the suture is tunnelled to the lateral aspect of the calcaneal bone and guided out through a 5 mm stab incision. A hole is drilled through the calcaneal bone 1 cm distal to the tendon insertion (exit through 5 mm stab incision medially). The PDS in guided though the hole. Now the mandarin is used to guide the suture back to the proximal site of the tendon. After the foot is placed in plantar flexion the suture is tied. After wound closure a cast is applied with the foot still in plantar flexion. After one week a tape bandage is applied for a total period of 6 weeks. In the first two weeks the tape bandage is supported by a 2 cm heel raise. The following 2 weeks the heel raise is reduced to 1 cm. The last two weeks the heel raise is removed (tape bandage will be renewed every time the heel raise is changed). Full weight bearing is allowed during the 6 weeks of tape bandage, not allowing sporting activities or walking stairs on tiptoes. Crutches are advised in the first week of casting, thereafter for maintenance of balance, but only if necessary.

**Figure 1 F1:**
[figure not shown]
Surgical repair technique. Taken from [7].

Conservative therapy consists of a cast in plantar flexion for one week. After one week a functional bracing system (Vacoped, Figure 2) [19] is applied for 6 weeks. The Vacoped bracing system (Company OPED, Valley, Germany) is a multifunctional splint consisting of several components. The essential parts are the dorsal and ventral shell, the vacuum cushion with changeable terry cloth covers, the belts with security locks and the removable sole. Prior to study use the brace was successfully used in a small pilot series and an instructions meeting on brace application was held in all participating hospitals. In the first two weeks the brace is fixed in 30° plantar flexion. The following 2 weeks in is in rigid 15° plantar flexion. The last two weeks the brace is dynamic from neutral position to 30° plantar flexion. Full weight bearing is allowed during the 6 weeks of bracing, not allowing sporting activities or walking stairs on tiptoes. Crutches are advised in the first week of casting, thereafter for maintenance of balance, but only if necessary.

**Figure 2 F2:**
[figure not shown]
Vacoped.

After tape or brace removal patients were advised further rehabilitation with physiotherapist and were allowed sports 3 months after rupture. Patients were free to choose their physiotherapist.

### Design of collection of data

#### Primary endpoint

complications other than re-rupture, i.e. infection, disturbed wound healing, sural nerve injury, scar adhesions, deep vein thrombosis and all other complications per treatment group.

During follow-up all complications will be documented by a surgeon or resident according to a standardised procedure using the definitions of complications presented in the Table 2. All complications will be included in the final analysis of results.

**Table 2 T2:** Definitions of complications used during follow-up.

**Complication**	**Definition**
Infection	Clinical signs of wound infection, i.e. redness, swelling, pain and functional impairment. Deep infection is defined as an infection beyond skin or subcutaneous fat needing surgical treatment in the operating theatre.
Disturbed wound healing	Keloid formation or hypertrophic scar, secondary wound healing, protruding PDS knot.
Sural nerve injury	Any sign of altered sensibility in the sural nerve area diagnosed by surgeon or surgical resident (using touch and pin prick test).
Scar adhesion	Clinical signs of adhesion of skin to underlying tissue layers. Clear wound retraction at ankle movement.
Deep vein thrombosis	Clinical and ultrasonographic signs of deep vein thrombosis of the ipsilateral lower leg.
Other complications	Any complication met during follow-up.

#### Secondary endpoint

re-rupturing (clinical diagnosis supported by ultrasound), time off work, sporting activity post rupture and patient satisfaction. The Thompson test is used for clinical diagnosis of re-rupture. Failure in plantar movement of the foot during calf muscle squeeze is considered a positive sign for re-rupture. Ultrasound evaluation for re-rupture is performed in neutral ankle position. Complete tendon rupture with tendon gap was considered a re-rupture. Time off work will be registered by a patient diary. Complete return to profession was used as endpoint. Stratification to type of profession (sedentary and non-sedentary) will be performed afterwards. A visual analogue scale (VAS) on patient satisfaction with treatment will be measured at 7 weeks, 3 and 12 month. Patient outcome will also be evaluated by the Leppilahti scoring method, a clinical scoring system, including subjective assessment of symptoms and evaluation of ankle range of motion and isokinetic measurement of ankle plantar flexion and dorsifexion strengths (Table 3) [20].

**Table 3 T3:** Leppilahti score.

**Clinical factors**	Scores (points)*

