#### Data analysis

The study groups will be compared for their baseline characteristics. The number of complications will be calculated for the primary endpoint. Distribution measures will be calculated for the secondary endpoints at the different moments of follow-up. Differences between groups for the number of complications and distribution of other endpoints will be calculated for each outcome measure with a 95% confidence interval. The study groups will be compared with the chi-square test for categorical outcome variables and the independent sample Student *t *test for continuous outcome variables. The dropouts and withdrawals will be summarized and analyzed by treatment groups. A listing of subject with withdrawal with the date and reasons for termination will be provided.

Because we standardised the intevention procedures we do not anticipate important differences between centers. So we do not stratify our primary analysis for center. However, when eventually differences may occur we will explore their effect in a secondary analysis (Mantel-Haenszel). All analysis in SPSS (SPSS Inc, Chicago Illinois).

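### Time off work ends with an event that can go unobserved, but the plan's general rule sends it to a t test, which cannot use a censored duration

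*Protocol article*

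**What the plan says.** Under Secondary endpoint, the protocol article defines time off work by a diary and by the event that closes the interval: "Time off work will be registered by a patient diary. Complete return to profession was used as endpoint". It adds a subgroup split: "Stratification to type of profession (sedentary and non-sedentary) will be performed afterwards".

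Under Data analysis, tests are assigned by type of variable. Categorical outcomes get a chi-square test. The rest get the "independent sample Student *t *test for continuous outcome variables". Differences between the groups "will be calculated for each outcome measure with a 95% confidence interval". Mantel-Haenszel appears only as a secondary look at centre differences. No method for time to an event is named.

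Three other statements bear on the point. The abstract says "Patient follow-up will be 12 month". The Sample size section allows for "an attrition rate of 10% we need to randomize at least 36 patients per treatment arm". The Design of analysis section commits to intention to treat.

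**The concern.** A duration in days is a continuous variable, so the general rule assigns it to the t test even though the endpoint section names no test. A t test needs a finished number for each patient. Two kinds of patient may not have one: those who withdraw before going back to work in full, and those still off work at 12 months.

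If the comparison is made in returners only, inclusion depends on an outcome that arises after randomisation. The absences removed at 12 months are by construction the longest ones. The estimated difference in days is then pulled toward zero whenever one arm has more long absences than the other, and the analysis no longer covers all randomised patients. What is at stake is mainly the estimate and its confidence interval, and to a lesser degree power.

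**Working it through.** The documents state no figure for this endpoint, so there is nothing of the plan's to reproduce. The check asks how much the choice of method could matter.

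**Inputs from the protocol article:** 36 patients per arm, 12 months of follow-up (taken as 365 days), 10% attrition.

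**Assumptions, not in the documents:** log-normal time to full return; medians of 90 v 60 days with log-SD 0.6, 0.9 or 1.2; also 30 workers per arm with log-SD 1.0 and medians of 60 v 30 or 60 v 33 days; a dropout time uniform over the year in 10% of patients; two-sided 0.05; no job strata. Each scenario has 8,000 simulated trials, so the Monte Carlo standard error of a power is at most √(0.25/8000) = 0.6 points.

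**Power**

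| Per arm, medians, log-SD | Return unobserved | t test, returners only | t test, 12-month non-returners set to 365 days | Log-rank |
|---|---|---|---|---|
| 36, 90 v 60, 0.6 | 3% | 72% | 73% | 73% |
| 36, 90 v 60, 0.9 | 7% | 33% | 39% | 41% |
| 36, 90 v 60, 1.2 | 12% | 17% | 24% | 26% |
| 30, 60 v 30, 1.0 | 4% | 57% | 61% | 68% |
| 30, 60 v 33, 1.0 | 4% | 46% | 49% | 56% |

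The loss of the returners-only t test against log-rank runs from about 1 point (72% v 73%) to about 11 points (57% v 68%). With equal medians of 60 days, every test rejected in about 5% of trials.

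**Estimate**

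The fair target is the difference in mean days off work within 12 months, which 12 months of data can identify. For a log-normal time with median m, μ = ln m and log-SD σ:

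E[min(T, 365)] = m·exp(σ²/2)·Φ((ln 365 − μ − σ²)/σ) + 365·[1 − Φ((ln 365 − μ)/σ)]

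Example with σ = 0.9:
- m = 90: 134.9 × 0.744 + 365 × 0.060 ≈ 122.3 days
- m = 60: 90.0 × 0.866 + 365 × 0.022 ≈ 86.1 days
- difference: 86.1 − 122.3 = −36.2 days

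| Medians, log-SD | Restricted difference | Difference in returners | Shrinkage |
|---|---|---|---|
| 90 v 60, 0.6 | −35.1 | −32.4 | 1 − 32.4/35.1 = 8% |
| 90 v 60, 0.9 | −36.2 | −26.6 | 1 − 26.6/36.2 = 27% |
| 90 v 60, 1.2 | −33.9 | −20.2 | 1 − 20.2/33.9 = 40% |
| 60 v 30, 1.0 | −42.7 | −33.8 | 1 − 33.8/42.7 = 21% |

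Smaller simulations of the widest-spread case put its shrinkage slightly lower, near 37%, so the upper end is about 40%.

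**The case against.** The strongest reply is that the plan never says non-returners will be left out. It promises intention to treat and an account of dropouts by group, and detailed missing-data rules may stand in an analysis plan that is not shown. A patient followed to 12 months and still off work has a usable value for days off work within 12 months. Coded that way, the t test recovers part of the loss: 61% against 68% for log-rank in the 60 v 30 scenario, and no gap at log-SD 0.6. This stands, and it limits the size of the point. It does not help patients who withdraw before returning, and the article does not define the endpoint as a restricted quantity. What the article does fix is a test that cannot take a censored value.

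A simple rank test on the recorded times also does slightly better than log-rank here (71% v 68% in the 60 v 30 scenario). But it treats censored times as complete, which is safe only if withdrawal is alike in both arms, and it gives no effect estimate.

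Some stronger readings are tempting but unsupported:

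- **Job type classified once outcomes are known.** The factor and its two levels are named in advance. Since "Randomisation is in blocks (4 blocks) and stratified by centre", with no mention of profession, the natural meaning of the later stratification is stratification at analysis. Nothing suggests late classification.
- **Strong skew, with desk workers back in days and manual workers in months.** The documents give no distribution of work absence by job. Skew is an assumption here, and at the mildest spread the power loss almost vanishes.
- **Most of the effect in days would be lost.** That follows only against an unrestricted mean difference (−61.6 days at log-SD 1.2), which 12 months of data cannot recover without extrapolation.

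**Conclusion.** The point holds in a limited form. The endpoint is a time to an event that may be unobserved, and the only rule that reaches it is a t test, which has no place for such patients. Under assumed log-normal times with about 3% to 12% of returns unobserved, restricting the t test to returners costs about 1 to 11 points of power and shrinks the mean difference by about 8% to 40% of its 12-month restricted value. With similar withdrawal in both arms, type I error stays close to 5%, so a reader should not infer a raised risk of a false positive finding. The t test applies through the general rule and is not named for this endpoint. The primary endpoint is untouched. This is a worthwhile but modest improvement to one secondary analysis.

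**What to change.** State in the Data analysis section that, for patients employed at injury, time to complete return to profession is analysed by Kaplan-Meier and a log-rank test stratified by the already planned sedentary/non-sedentary factor. Censor at the last diary entry or at 12 months, whichever comes first. Report median times and either a hazard ratio or a 12-month restricted mean difference, with a 95% confidence interval. The restricted mean keeps the result in days and does not need proportional hazards. Keep the t test for continuous outcomes that are not subject to censoring.

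The cost is a few lines of analysis wording, using the diary data already planned. The simple difference in mean days becomes descriptive. The new analysis still assumes that withdrawal is unrelated to the time of return, which the planned listing of withdrawals with dates and reasons can help to judge.
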